## Abstract

**Introduction:**

Neck pain (NP) is a leading cause of disability worldwide and affects more than 200 million people. Incidence and associated economic burden are constantly increasing, and little is known about the factors that promote new and more severe episodes in those individuals with recurrent NP. Current evidence supports that changes in physical, psychological and social factors persist between NP episodes, and these changes might contribute to the development of new episodes. The End Recurrent Neck Pain (END-RNP) study aims to use physical, psychological and social factors tested while in symptom remission to predict, within a 12-month period, the frequency and severity of new NP episodes.

**Methods and analysis:**

The END-RNP study is a multicentre, prospective cohort study conducted from March 2025 to February 2028 at the University of Birmingham and the University of Essex (UK). 300 adults reporting two or more NP episodes in the previous year will be recruited from September 2025 to form the recurrent NP cohort, and 48 adults without a history of NP will provide normative data. Laboratory testing will be conducted for all participants when pain-free by assessing cervical kinematics and proprioception, neck-muscle strength, endurance and activation, pain processing, psychological and social factors. All recurrent NP participants will complete online questionnaires every 2 weeks for 12 months, recording days with NP, pain intensity/interference, healthcare use and other behavioural and environmental factors. Participants in the recurrent NP cohort who experience an acute NP episode during the 12-month follow-up will repeat the laboratory assessment. To develop the prediction models, candidate predictors will be the baseline measurements of any feature that shows either cross-sectional differences between recurrent NP and control groups or within-subject changes between the pain-free baseline and a pain episode. From the identified candidate predictors, two multivariable models will be developed using penalised regression, with (i) number of days with NP (linear regression) and (ii) NP severity (ordinal regression) as their respective dependent variables. Internal validation will use bootstrap resampling to estimate optimism-adjusted performance (R^2^, C-statistic and calibration slope), prediction instability and uncertainty, and clinical utility. The models from the END-RNP study will provide clinical prediction tools to help identify those at high risk of frequent and severe NP episodes and to inform the personalised prevention of recurrent NP.

**Ethics and dissemination:**

The END-RNP study was approved by the Ethics Committee at the University of Birmingham (ERN_4005-Aug2025) and by the University of Essex (ETH2526-0098) on 2 September 2025, prior to the recruitment of the first participant. The findings will be presented at national and international conferences and submitted for publication in peer-reviewed journals.

STRENGTH AND LIMITATIONS OF THIS STUDYThis study will adopt a comprehensive biopsychosocial approach, including physical, psychological and social factors as potential predictors of future neck pain episodes within a longitudinal design.This study will be powered for the development of clinical prediction models and will use robust statistical methods for development, predictor selection and internal validation in accordance with established guidelines.The extensive and frequent follow-up will enable us to capture the temporal dynamics and episodic nature of recurrent neck pain.The developed models will be based on data collected in the UK. Further validation in new samples will be required to examine generalisability and transportability of the findings.All data will be collected within a laboratory setting; therefore, the generalisability of the findings and the feasibility of applying them in routine clinical settings will need to be investigated.

## Introduction

 Neck pain (NP) remains one of the leading causes of disability worldwide, resulting in financial burden and poor quality of life.^1 2^ In the UK, NP is second only to low back pain across the musculoskeletal causes of disability.^3^ While the total number of cases has risen with population growth and ageing, the global age-standardised incidence rate has also increased significantly since the early 2010s,^4^ with data from 2020 showing that more than 203 million people suffered from NP.^5^ This figure is expected to grow by more than 30% over the next three decades.^5^ Of those who experience an episode of NP, between 50 and 85% will report NP 1–5 years later,^6^ with over 20% of people developing recurrent pain episodes.^7^ Despite being a research priority,^8^ the factors contributing to the development of new episodes of NP remain poorly understood.^8^ Understanding these factors would allow targeted interventions and preventative measures.

People with NP present with impairments in physical, psychological and social function that may predispose them to ongoing pain or recurrence, as described by theories linking motor adaptations and psychosocial factors to pain.^9 10^ Clinical studies and systematic reviews have reported restricted range and speed of neck movement,^11 12^ poor quality of neck movement,^13 14^ altered muscle behaviour and sensorimotor control deficits^15 16^ in people with chronic or recurrent NP. Importantly, in individuals with recurrent NP, the resolution of pain symptoms does not necessarily correspond to a recovery of physical function; sensorimotor impairments similar to those observed in chronic NP often persist during symptom remission,^17^ potentially acting as a predisposing factor for future NP episodes. Lower pain pressure thresholds and altered conditioned pain modulation identified in people with NP also suggest impairment of central pain-modulating systems.^18 19^ The potential contributors to new NP episodes are not limited to physical factors, as psychological variables such as anxiety, stress, depression and low self-efficacy, along with social factors, can further modulate the pain experience.^20^,^23^ For example, social support, job satisfaction and other work-related factors have been associated with the development of NP.^24^ Given this multidimensional interplay, it is unlikely that any single factor explains NP recurrence; instead, complex interactions across domains could result in new NP episodes. Indeed, previous studies demonstrated how physical and psychological factors are highly interrelated in people with chronic and recurrent NP.^25 26^

Advancing the understanding of NP recurrence requires methodological approaches that acknowledge the multidimensional nature of NP, encompassing physical, psychological and social factors, and which employ methodologies capable of managing such complexity while monitoring NP progression over time. Although previous research has examined multiple domains within a biopsychosocial framework,^27^ individual and contextual physiological responses to pain have received less attention.^28^ Previous studies have predominantly focused on patient-reported outcomes, exploring what patients perceive and how they relate to their health condition, with limited attention to physical impairments associated with NP.^27 28^ In a recent systematic review, we found only six studies investigating predictors of recurrent NP episodes, with low quality of evidence and contrasting findings across studies for physical factors, and some limited evidence supporting the predictive role of psychological distress.^29^ However, a limitation of previous studies was the lack of a clear distinction between recurrent and chronic NP. While chronic NP involves persistent symptoms, recurrent NP is characterised by distinct episodes of pain separated by symptom-free remission periods. This makes it challenging to distinguish between the two if outcomes are evaluated at a single time point, overlooking the different symptom trajectories of recurrent versus chronic NP.^30^ Additionally, previous studies have typically assessed participants at baseline while in pain. Testing during an acute painful episode can introduce significant heterogeneity, as the presence of pain alters physical function and psychological states,^10 31 32^ potentially masking the role of relevant prognostic factors. Therefore, recruiting and testing individuals with recurrent NP during a pain-free remission period provides a more homogeneous sample. This allows for the identification of predictors of recurrence without the confounding influence of current pain. Evidence from patients with whiplash-associated disorders tested during a pain remission period suggests that physical impairments may predict future NP episodes.^33^ However, whiplash-associated disorders and idiopathic NP differ in aetiology and have been shown to present distinct physical and sensorimotor profiles.^34^,^36^ As such, findings from people with whiplash-associated disorders may not fully generalise to non-traumatic neck pain, highlighting the need to directly investigate prognostic physical factors in individuals with recurrent idiopathic NP. A comprehensive, multidimensional approach is therefore essential to address specifically the complexity of idiopathic NP and identify predictors of new NP episodes, while recognising the fluctuating and recurrent nature of NP, characterised by periods of symptom exacerbation and remission.^37^

### Aims and objectives

The primary aim of this study will be to develop and internally validate clinical prediction models for use in individuals with recurrent idiopathic NP to predict, within 12 months, the frequency and severity of new NP episodes using physical, psychological and social factors. This will be accomplished through two main objectives:

*O.1 Identify potential candidate predictors*. We will first identify potential candidate predictors by examining how neuromuscular control, neck function, pain processing, psychological and social features in individuals with a history of recurrent NP episodes differ from those in a control group without a history of NP, and how these components are affected during an acute new NP episode. By identifying clinically relevant features that change due to pain – whether they differ in people with a history of recurrent NP during remission compared with a control group, or whether they worsen during a new pain episode – this will aid in selecting potential candidate predictors. We hypothesise that some potential predictors of future NP episodes are those influenced by pain, either because they remain altered during pain remission when compared with a control group without history of NP, worsen during a new NP episode or both. In addition, the selection of candidate predictors will be informed by evidence from recent systematic reviews on prognostic factors for recurrent or persistent NP.^28 29^

*O.2 Prediction model development and internal validation*. Based on findings from the first objective, we will use the identified candidate predictors from the physical, psychological and social domains to develop two prediction models, followed by internal validation. These models will estimate the number of future days with NP and the severity of new NP episodes over 12 months.

## Methods

The END-RNP study is a multicentre prospective longitudinal cohort study; it is registered on the Central Portfolio Management System (CPMS ID: 69289) and receives support from the NIHR Research Delivery Network. This study will be conducted at the University of Birmingham, UK and University of Essex, UK from March 2025 to February 2028. The study will be reported according to the STROBE checklist and statement for transparent reporting of clinical prediction models that use regression or machine learning methods (TRIPOD+AI).^38 39^ A summary of the flow of the study is presented in figure 1. This study design has been informed by our Patient and Public Involvement and Engagement (PPIE) group. Specifically, the group provided feedback on the appropriate frequency and length of follow-up questionnaires, offered strategies to maximise participant engagement and helped identify potential predictors of spinal pain based on their lived experiences.

**Figure 1 F1:**
[figure not shown]
Study flow. NP, neck pain.

### Participants and recruitment

We will recruit male and female participants aged between 18 and 70 years. This upper limit is chosen to balance the inclusion of a wide adult age range against the confounding influence of advanced, age-related degenerative pathologies, whose prevalence and severity increase markedly in older populations.^40^ People reporting a history of recurrent episodes of NP but in remission (ie, pain-free) at the time of recruitment will be included in the recurrent NP cohort, and those without a history of NP will also be recruited as a control group to address the objective O.1. Inclusion criteria for the recurrent NP cohort will be the experience of two or more episodes of NP of idiopathic origin lasting more than 24 hours during the previous 12 months, separated by a period of remission, and with pain intensity greater than 2 on an 11-point numerical rating scale.^41^ People with recurrent NP tested during a period of remission need to be pain-free over the prior 30 days. The control group will include adults with no history of neck or shoulder pain that limited their daily function. Individuals will be excluded from both groups if they report chronic NP (ie, pain in the NP region from more than 3 months) or an acute episode of NP at time of recruitment, previous shoulder or spinal surgery, history of neck trauma, cervical radiculopathy/myelopathy, previous fracture in the neck or shoulder region, spinal deformity, neurological or cardiovascular disorders, rheumatic joint disease, possibility that they might be pregnant or any contraindications to physical exertion. Recruitment will be conducted between September 2025 and December 2026.

Participants with recurrent NP will be recruited from the community in Birmingham and in Essex. The recruitment process will aim to reflect the real-world distribution of NP occurrences between sexes. Given the 2:1 ratio of NP prevalence in favour of females,^42^ we expect that the recruitment process will result in a proportional sample that mirrors this difference. Due to the use of questionnaires and standardised procedures in the evaluation of candidate predictors and outcomes, only people able to understand or follow study procedures will be recruited. Participants for the control group will only be recruited from the community in Birmingham, and we will ensure comparable demographic characteristics to those within the recurrent NP cohort. Participants will be recruited from the University of Birmingham and University of Essex staff/student population and Birmingham’s/Essex’s local community. Recruitment methods will include printed hard copy advertisements with researchers’ emails pasted throughout the campus within the University of Birmingham and University of Essex, and identical soft copy advertisements disseminated using the University’s intranet and email system, social media platforms such as Facebook and *X,* and via word of mouth. Additionally, NIHR Research Delivery Network support will allow us to recruit participants with recurrent NP through the NIHR 'Be Part of Research’ service.

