### Prognostic variables of pain recurrences

#### Baseline laboratory assessment

All recruited participants with a history of recurrent NP episodes will attend an initial laboratory session (in Birmingham or Essex) during a period of symptom remission, and a battery of tests will be conducted to obtain a comprehensive evaluation (table 1). To minimise inter-site variability, all assessments will follow a standardised protocol, and both laboratories will use identical equipment from the same manufacturer. Participants will also be asked to complete a series of questionnaires to assess psychological features, including the Depression, Anxiety and Stress Scales (DASS-21),^43^ the short version of the Tampa Scale for Kinesiophobia (TSK-11),^44^ the EQ-5D-5L^45^ and pain processing characteristics, including the pain-self efficacy questionnaire,^46^ pain coping inventory^47^ and central sensitisation inventory.^48^ Overall, we will collect information on demographic characteristics, psychological and social factors, pain processing, neck kinematics, neck sensorimotor control and neck muscle function.

**Table 1 T1:** Collected data within physical, psychological and social domains

Domain	Feature extracted	Measurement tool
Demographics and Neck Pain characteristics	Age Sex BMI Ethnicity Number of other pain sites Number of previous pain episodes	Single question for each feature
Psychosocial factors	Stress (0–21) Anxiety (0–21) Depression (0–21) Kinesiophobia (11-44) Quality of life (0–100) Occupation Education level	DASS-21 DASS-21 DASS-21 TSK-11 EQ-5D-5L Single question Single question
Pain processing	Self-efficacy (0–60) Pain coping (12–48 active, 22–84 passive) Central sensitisation (0–100) Pressure pain threshold (kPa) Conditioned pain modulation	Pain Self-Efficacy Questionnaire Pain Coping Inventory Central sensitisation inventory Pressure algometry Cuff pressure algometry
Kinematic features and sensorimotor control	Average range of neck motion in flexion-extension, lateral flexion (R/L), rotation (R/L) Average speed of neck movement in flexion-extension, lateral flexion (R/L), rotation (R/L) Smoothness of neck movement (Jerk Index) in flexion-extension, lateral flexion (R/L), rotation (R/L) Neck proprioception (joint reposition error during right and left rotation)	All features obtained using wearable Inertial Measurement Unit (IMU, Sensamove 3D Cervical Trainer)

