### Outcomes of interest

The development of new NP episodes and their severity represent the main outcomes of interest in the recurrent NP cohort. To define the presence and severity of NP episodes, multiple questions will be collected through online questionnaires and by referring to the previous 2 weeks recall period (table 2). The collected information will be used to identify the number of days with NP during the 12-month follow-up. Furthermore, average and worst pain intensity (rated using a visual analogue scale 0–100) during new NP episodes over the 12 months will be aggregated to define the severity of NP. Based on established cut-points for grading chronic musculoskeletal pain,^72^ participants will then be classified into four severity groups: No pain (score of 0), mild pain (score of 1–34), moderate pain (score of 35–64) and severe pain (score >64). These two continuous and ordinal outcomes (ie, days with NP and severity of NP) will be the dependent variables used to develop the prediction models. Although we recognise that some participants might develop chronic pain during the follow-up, we decided to specifically focus on the frequency and severity of new NP episodes to better fit the fluctuating nature and symptom trajectory of people with recurrent NP.

**Table 2 T2:** Collected data on neck pain recurrences

Domain	Features extracted	Measurement tool
Recurrent episodes	Number of days with NP Average and worst NP intensity (VAS, 0–100) NP interference in daily activities (VAS, 0–100) NP interference in recreational, social and family activities (VAS, 0–100) NP interference with work (VAS, 0–100) Number of days using medication for NP relief Number and type of treatment received	Single questions

NP, neck pain; VAS, visual analog scale.

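### Table 1 records no past-year pain intensity or days with neck pain, the nearest baseline counterparts of the two outcomes, and the O.1 tests cannot sensibly judge any pain-history variable

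*Protocol article*

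**What the plan says.** **Outcomes.** Outcomes of interest names two dependent variables: the number of days with NP over the 12-month follow-up, and a four-level severity grade. For the grade, average and worst intensity "during new NP episodes over the 12 months will be aggregated to define the severity of NP".

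**Entry.** Participants and recruitment requires "two or more episodes of NP of idiopathic origin lasting more than 24 hours during the previous 12 months", "with pain intensity greater than 2 on an 11-point numerical rating scale". Of the controls it says: "The control group will include adults with no history of neck or shoulder pain that limited their daily function".

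**Baseline data.** The first row of Table 1 reads "Age Sex BMI Ethnicity Number of other pain sites Number of previous pain episodes". No other row concerns past neck pain. The questions on days and intensity appear in Table 2, which covers follow-up.

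**Candidate selection.** The abstract defines the candidates as the baseline measurements of "any feature that shows either cross-sectional differences between recurrent NP and control groups or within-subject changes" between remission and an episode. The O.1 analysis section repeats this rule for physical, psychological and social features. Aims and objectives adds that systematic-review evidence on prognostic factors will inform the selection. The O.2 section says that the candidates include those found in O.1, which is not closed wording.

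**The concern.** The previous value of an outcome is a natural candidate predictor of its next value. Here the previous values would be how intense the past year's episodes were and how many days they took up. The first has no entry in Table 1. The second is covered only indirectly, by the number of episodes.

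Two things are at stake. If past severity carries prognostic information, the severity model has no direct access to it, and a laboratory or psychological feature that merely tracks past severity may be credited with the prediction. The study also could not show what the laboratory battery adds to asking how bad the last year was. The Discussion looks ahead to a reduced predictor set for routine practice and to predictors as possible treatment targets, so both matter for how the models are used.

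This cannot be left to a later analysis plan. A value that was not recorded at baseline is not available to any analysis, and recruitment runs from September 2025 to December 2026.

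**Working it through.** **1. Outcomes against Table 1**

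| Outcome | Nearest baseline counterpart | In Table 1? |
|---|---|---|
| Days with NP over 12 months | Days with NP in the past 12 months | No; number of previous episodes is a partial substitute |
| Severity from average and worst intensity | Usual or worst intensity of past-year episodes | No |

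**2. The O.1 tests applied to pain history**

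- *Comparison with controls.* Controls have no history of function-limiting neck or shoulder pain, while the cohort has at least two qualifying episodes. Past intensity or duration is either undefined in controls or, if coded zero, differs because of how the groups were chosen. Neither result bears on prognosis.
- *Remission against episode.* A past-year value is not a state that an acute episode alters. At most the new episode is added to the tally.
- The same holds for the number of previous episodes, the one neck-pain history item that is collected.

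**3. The plan's own parameter budget**

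Inputs from the sample size section: n = 250, R² = 0.40, residual SD 15, shrinkage S ≥ 0.9, optimism in R² ≤ 0.05. With p parameters,

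S = 1 + (p − 2) / {n · ln[1 − (R²(n − p − 1) + p)/(n − 1)]}.

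For p = 16 and n = 250: (0.40 × 233 + 16)/249 = 0.4386; ln(0.5614) = −0.577; S = 1 − 14/(250 × 0.577) = 0.903. The minimum n is 242 for shrinkage, 1 + 16 × 0.60/0.05 = 193 for optimism, and 234 + 16 = 250 for the residual SD. The largest is 250, so the stated figure of about 16 candidates is reproduced.

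For the severity outcome collapsed to two equal categories, the maximum R² is 0.75, so a Nagelkerke value of 0.4 corresponds to 0.30. Ten parameters need 10 / [0.1 × −ln(1 − 0.30/0.9)] = 247, consistent with the stated 10 at n = 250.

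**4. Room for the history variables**

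- Within the 16, n stays at 250.
- Two added on top (p = 18, linear terms) give S = 0.891 at n = 250, and S ≥ 0.9 would need n = 277.
- In the collapsed severity model, 12 parameters instead of 10 need 296 instead of 247.

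The variables should therefore take places within the budget.

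**5. Possible gain**

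The document gives no correlation between past and future NP, so r below is an assumption: the partial correlation of past value with outcome, given the other predictors. New R² = 1 − (1 − 0.40)(1 − r²), and new residual SD = 15 · √(1 − r²).

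| r | R² | Residual SD (days) |
|---|---|---|
| 0 | 0.40 | 15.0 |
| 0.2 | 0.424 | 14.7 |
| 0.3 | 0.454 | 14.3 |
| 0.4 | 0.496 | 13.8 |

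**The case against.** A reader might infer that past intensity and duration cannot become candidates and that neither model will use them. The document does not support that. Aims and objectives lets systematic-review evidence inform selection, and the O.2 section does not confine candidates to O.1 features. If controls were coded zero, such variables would pass the group comparison trivially rather than fail it. Episode count also sits in Table 1 under the prognostic variables although controls have no natural value for it, which suggests that pain history was not meant to depend on O.1 alone. This objection stands. What remains is that the abstract reads as closed, and that the open route needs recorded values.

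A reader might also infer that eligibility screening already yields both values. It does not. Screening needs only thresholds on episode duration and intensity, the article does not say that numbers are stored, and total past-year days is not asked at all.

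Three further points carry weight. Episode count gives part of the frequency history, so outcome history is not wholly absent. The plan chose two-week recall to limit recall bias, and a 12-month recall item is more exposed to it. The stated aim is to develop and internally validate models, so the lack of a history-only comparison contradicts nothing. The full protocol may hold more baseline items, but Table 1 is presented as the collected data and reads as a feature list.

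**Conclusion.** The point holds as a gap in baseline measurement and a mismatch between the selection rule and one class of variable. Table 1 has no past-year intensity and no past-year days. The gap is clear for severity and partial for days. The O.1 tests cannot inform the choice of any pain-history variable, including the episode count that is collected, and the selection passages need reconciling.

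It does not follow that the plan bars outcome history from the models, or that they will perform poorly without it. The size of any gain is unknown: across assumed partial correlations of 0 to 0.4, R² would lie between 0.40 and 0.50 and residual SD between 15 and 13.8 days. That range includes no gain, and it takes the planned R² of 0.40 as the value without these items, which the document does not state. The case for changing rests on low cost and on the fact that unrecorded values are lost to later analysis.

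**What to change.** 1. Add to Table 1, for the recurrent NP cohort, a numeric usual or worst intensity of past-year episodes. Screening already applies a threshold, so the number itself should be stored.
2. Add one new single question on approximate days with NP in the past 12 months.
3. Pre-specify past intensity (severity model), past days (days model) and number of previous episodes as candidates outside the O.1 tests and within the 16 parameters. They then stay on the candidate list in every bootstrap repetition.
4. Align the abstract and the O.1 section with Aims and objectives and the O.2 section, stating how a variable that O.1 cannot test becomes a candidate.
5. Fit a history-only model for each outcome and report the full model's gain in optimism-adjusted R² (days) and C-statistic (severity).

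Cost: one or two short questions, one or two of the 16 places in each model, and one simple extra model per outcome. Past-year answers carry 12-month recall error. Anyone already enrolled whose values were not stored would need a brief follow-up question or multiple imputation. The target of 250 analysed participants does not change.

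### The written control criterion is looser than the stated control group and does not make the two groups mutually exclusive, which could bias the O.1 between-group differences toward zero

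*Protocol article*

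**What the plan says.** The protocol article describes the control group in two ways.

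- **Descriptive.** The abstract states that "48 adults without a history of NP will provide normative data". Aims and objectives sets O.1 up as a study of how features in people with recurrent neck pain "differ from those in a control group without a history of NP". Participants and recruitment begins the same way: "those without a history of NP will also be recruited as a control group to address the objective O.1".
- **Operative.** Later in Participants and recruitment, the sentence that functions as the control inclusion criterion reads: "The control group will include adults with no history of neck or shoulder pain that limited their daily function".

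The recurrent cohort needs "two or more episodes of NP of idiopathic origin lasting more than 24 hours during the previous 12 months", separated by remission, "with pain intensity greater than 2 on an 11-point numerical rating scale". When tested in remission, these participants "need to be pain-free over the prior 30 days". Functional limitation is not part of the cohort definition.

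As regards neck pain episodes, the exclusions common to both groups remove chronic neck pain and an acute episode at recruitment. They do not remove past episodes that have resolved.

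Under Data analysis plan, O.1, a feature that differs between cohort and controls, or within a person between remission and a pain episode, becomes a candidate predictor.

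**The concern.** The two descriptions define different populations. Having no history of neck pain is a stricter condition than having no history of neck pain that limited function. The two groups are also separated on different axes: controls by the functional effect of past pain, the cohort by number, duration and intensity of episodes. Nothing in the written criteria stops one person from satisfying both.

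What is at stake is the O.1 comparison. The Introduction and the aims rest on the premise that alterations persist in remission. If so, controls with recurrent-type episodes would carry some of the same alterations. The normative values would move toward the cohort, the between-group differences would shrink, and some features that truly differ could fail to show it.

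**Working it through.** **1. Overlap of the criteria.** Take a person with two idiopathic 30-hour episodes in the past 12 months, separated by remission, each 3/10, neither limiting daily function, now pain-free for more than 30 days.

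| Requirement | Met? |
|---|---|
| Cohort: at least two idiopathic episodes in 12 months | yes |
| Cohort: more than 24 hours each | yes (30 h) |
| Cohort: intensity above 2 | yes (3) |
| Cohort: 30 days pain-free | yes |
| Control: no function-limiting neck or shoulder pain | yes |
| Shared exclusions: chronic neck pain, or acute episode at recruitment | neither applies |

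The person meets both sets of written criteria but does not fit the descriptive label for controls.

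**2. The plan's own sample size.** Inputs from Sample size estimation (O.1): d = 0.5, alpha 0.05, 2:1 allocation, 48 controls and 96 recurrent participants. The 0.8 printed there as beta is read as power. Using the two-sided t-test and the noncentral t distribution:

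- noncentrality = d / √(1/n₁ + 1/n₂), df = n₁ + n₂ − 2
- 48 and 96: √(1/48 + 1/96) = 0.1768; 0.5 / 0.1768 = 2.83; df = 142; power 0.802
- 47 and 94: power 0.794

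So 48/96 reproduces as the smallest 2:1 design reaching 80%. The arithmetic is sound and carries no reserve.

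**3. Hypothetical dilution.** Let q be the share of controls whose mean equals that of the recurrent group. The document gives no value for q, so the values below are assumptions. The expected difference becomes d(q) = 0.5 × (1 − q).

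| Assumed q | d(q) | Power, 48 vs 96 | Power, 48 vs 300 |
|---|---|---|---|
| 0 | 0.50 | 0.802 | 0.894 |
| 5% | 0.475 | 0.761 | 0.861 |
| 10% | 0.45 | 0.715 | 0.823 |
| 20% | 0.40 | 0.613 | 0.728 |
| 30% | 0.35 | 0.503 | 0.612 |

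Allowing for the extra variance of a mixed control group changes little: 0.712 at 10% and 0.607 at 20% for 48 versus 96.

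The last column is shown because baseline laboratory testing covers all recurrent participants and 300 are to be recruited, although the O.1 sample size section plans the comparison on 96.

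**4. Cost of simply dropping affected controls.** At d = 0.5 with 96 recurrent participants, losing 5 controls (43 left, about 10%) gives power 0.77. Losing 10 (38 left, about 20%) gives 0.74.

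**The case against.** The strongest reply is that the paragraph should be read as a whole. It first allocates by history: people reporting recurrent episodes go to the cohort and people without such a history become controls. The functional-limitation sentence may only be meant to keep trivial aches from disqualifying a control. On that reading, a person with two recent episodes of more than 24 hours would be sent to the cohort. This is a fair account of the likely intention, but it does not settle the text. If having no history of neck pain applies as a separate condition, the functional qualifier does no work for neck pain. If the qualifier does work, the abstract and aims are inaccurate. Either way, the sentence on whom the group will include is the one a recruiter would apply.

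Three further objections stand and limit the point.

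- **The size is assumed.** The document does not say how common non-limiting neck pain is among controls. The calculation also gives every affected control the full recurrent-group mean. Someone with one old, mild episode also passes the criterion and need not resemble the cohort.
- **More data may be used.** With all 300 recurrent participants, power would still be 0.82 at an assumed 10%.
- **The route to the models is indirect.** Controls do not enter the prediction models. A feature missed here can still become a candidate through the within-subject comparison or through systematic-review evidence.

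A reader might infer that the 80% power claim fails, or that the normative data will be contaminated. The document supports neither. It shows that the criteria permit such controls, not that any will be enrolled or how many.

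**Conclusion.** The contradiction and the overlap follow directly from the text and need no assumption. The direction of any bias, toward no difference, rests on the study's own premise that impairments persist in remission. Its size cannot be determined. The illustrative fall from 0.80 to about 0.72 or 0.61 (48 versus 96), or to 0.82 or 0.73 from 0.89 (48 versus 300), holds only if 10% or 20% of controls had the full recurrent-group mean.

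This should be fixed. It affects the between-group arm of O.1 and the normative label given to the controls. Its effect on the prediction models is indirect, and the planned sample size is correctly calculated for the groups as described.

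**What to change.** Use one control definition in the abstract, aims and eligibility text.

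- **Definition.** Preferably make the criterion match the description, that is, no history of neck pain. If a threshold for trivial neck pain is kept, state it with its look-back period and align the abstract and aims with it.
- **Shoulder pain.** Keep the existing condition. A rewrite in terms of neck pain episodes alone would lose it.
- **Mutual exclusivity.** State that anyone with past neck pain episodes of the recurrent-cohort type cannot be a control, whether or not function was limited.
- **Controls already enrolled.** Table 1 includes an item counting previous pain episodes, and the same laboratory assessment is applied to controls, so past history may be at least partly checkable from data held. Replace controls who do not meet the definition, or omit them in a sensitivity analysis of the O.1 comparison. Removing them without replacement costs power, as shown in the working.

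The cost is one amended eligibility line, one extra screening question and possibly slightly slower control recruitment. Recruitment is planned to run to December 2026, so an early correction limits the number of controls to check or replace.
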